### Follow-up of patients

After inclusion, all patients will be followed for two years in total. Patients will visit the outpatient clinic after two weeks, six weeks, three months and one year. After two years an interview by telephone and written survey will be conducted to evaluate two-year functional and mechanical outcome. In the operative group follow-up starts on the day of surgery. For the non-operative group this is the day of inclusion (see Table 1).

**Table 1 T1:** Flowchart Sleutel-TRIAL

Date									
Visit	1 Emergency Room (ER)	2 Phone call 48 hours after ER visit	3 † First visit (pre- operative care)	4 † Operation	5 2 weeks	6 6 weeks	7 3 months	8 1 year	9 2 years
Eligible? (checking in- and exclusion	•								
criteria)									
Patient information	•								
Obtaining Informed Consent		•	• ^2^		• ^2^				
Randomisation (operative vs. non-		• ^1^							
operative treatment)									
Case Record Form + Randomisation form			•						
Preparing patient for operation			•						
(aneasthesia i.e.) †									
Peroperative Form †				•					
X-rays	• ^3^			•	• ^4^	• ^3^	•	•	
Follow-up Forms					• ^5^	• ^5^	• ^5^	• ^5^	
DASH-score					•	•	•	•	
SF-36 score (Quality of Life)					•	•	•	•	
Constant score (+MicroFET2)						•	•	•	
Telephone interview and written survey									•

• 1: obtaining Informed Consent (verbally) for randomisation and planning of clinic visit

• 2: obtaining definitive written Informed Consent

• 3: X-rays: AP-view and 30 degrees cephalad view

• 4: Panorama view

• 5: Forms for the corresponding visit

†: only for participants allocated to operative treatment

At each hospital visit various intrinsic (patient-related) and injury-related variables are collected. As part of standard care, X-rays are taken at admission and each follow-up moment. The X-rays are performed in anterior-posterior view and 30° caudocephalad view. After two weeks an X-ray of the contralateral shoulder is taken for comparison with the affected shoulder. The DASH outcome measure and SF-36 are filled out by the patient after two weeks, six weeks, three months and one year. The Constant score of both shoulders is determined after six weeks. The Constant score of the affected shoulder is also determined after three months and one year. The functional tests are performed by a single-blinded researcher or other single-blinded qualified personnel. During these tests, the patients have a sticker on the affected shoulder and they are not allowed to tell the examiner which therapy they have undergone. Furthermore, at each visit the researcher collects medical information according to the follow-up list (i.e., complications/adverse events, secondary interventions). Serious adverse events will be reported directly.

### Sample size calculation

Based on a non-union difference of 15 percent in a previous study [9], the sample size of 175 patients per treatment group was calculated with a power (1-β) of 80 percent and a type I error (α) of 5 percent, allowing for 12 percent drop-out. In total 350 patients will be included.

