### Current treatment concepts

Midshaft fractures have traditionally been treated non-operatively, even when substantially displaced [8]. The non-operative treatment strategy was based on early reports suggesting that clavicular non-unions are very rare. Clavicular mal-union, if present, was reported as being of radiographic interest only, without clinical importance [9]. Moreover, surgical treatment of acute midshaft fractures was not favoured due to relatively frequent and serious complications such as infection, non-union, pin migration, broken plates, and necessity of removal of hardware [2]. However, the prevalence of non-union or mal-union in dislocated midshaft clavicular fractures after conservative treatment is higher than previously presumed and fixation methods have evolved. Of all midshaft clavicular fractures, about two-thirds end up having some degree of mal-union [5]. Recent studies reported a non-union rate up to 15 percent and more [10,11,4] and a potential 20 to 25 percent decrease in shoulder function and arm strength [4,12,11-17].

The currently described indications for surgical treatment are open fractures, neurovascular involvement, skin compromise and wide separation of bone fragments with soft tissue interposition. Initial clavicular shortening exceeding 20 mm is upcoming as an indication for operative treatment, because shortening caused by dislocation has been associated with potential shoulder dysfunction [18,12]. An associated floating shoulder, or a scapular neck fracture, are relative indications for operative treatment of the clavicular fracture. Non-union and mal-union are mentioned as a delayed indication for operative treatment. If an operation is considered for displaced midshaft clavicular fractures, the preferred method of fixation is reduction and internal fixation by means of wires, pins, or plates with screws.

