### Recruitment, consent and randomisation

All eligible persons presenting at the Emergency Department (ED) or at the outpatient clinic with a new, dislocated midshaft clavicular fracture are informed about this trial. They receive information and a consent form from the attending physician, the physician assistant or the clinical investigator. After written informed consent has been obtained, the patient is randomised for either operative therapy with a plate fixation or for non-operative therapy. Minimisation randomisation is accomplished via the trial website using TenALEA (Trans European Network for Clinical Trials Services), an online registration and randomisation program. All patients are randomly allocated to one of the two treatment arms in a 1:1 ratio in each participating hospital. For each subsequent participant the allocation depends on the included participants to minimise the imbalance [29].

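### At the non-union rates the article supports, 175 patients per arm gives about 94–99.9% power for a 15-point difference, not the stated 80%

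*Protocol article*

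**What the plan says.** The Sample size calculation section of the protocol article contains the whole justification:

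- Target and result: "Based on a non-union difference of 15 percent in a previous study [9], the sample size of 175 patients per treatment group was calculated".
- Error rates: "with a power (1-β) of 80 percent and a type I error (α) of 5 percent". Sidedness is not stated.
- Attrition: "allowing for 12 percent drop-out".
- Total: "In total 350 patients will be included".

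The section on recruitment and randomisation gives the allocation: "All patients are randomly allocated to one of the two treatment arms in a 1:1 ratio". The primary outcome is the incidence of non-union, a binary endpoint.

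The calculation names no non-union rate for either arm. The only guidance is in the Background. For non-operative treatment, under Current treatment concepts: "Recent studies reported a non-union rate up to 15 percent and more". For primary plating, the same part of the article describes studies in which union was usual and complications few, without a figure. The previous trial on which the 15 percent rests is described there by its arm sizes and the direction of its result; its non-union rates are not shown.

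**The concern.** For two proportions, the number needed to detect a given absolute difference depends on where the rates lie. It is smallest when one rate is near zero and grows as both move towards 50%. Non-union after plating is described as uncommon, so a 15-point difference should need well under 175 per arm at 80% power.

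Sufficient power is the article's own reason for running a new trial, and non-union is the primary outcome. A reader of the sample size section will take 15 points as the difference this trial detects with 80% power. If it has 80% power for something appreciably smaller, that changes how a non-significant result should be read. If 15 points really is the target, the 80% figure is wrong and more patients are randomised than the target requires.

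**Working it through.** **Inputs from the article:** difference 15 percent, read as percentage points; power 80%; α 5%; drop-out 12%; 175 per arm; 1:1 allocation.

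**Assumptions:** two-sided α (z = 1.960; z for power = 0.8416). Operative non-union 0–10%, hence non-operative 15–25%, as a reading of the Background.

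**Step 1, evaluable patients.** 175 × 0.88 = 154 per arm, and 154 / 0.88 = 175 exactly. The planned calculation should therefore return about 154. If drop-out was instead added as a multiplier, 175 / 1.12 = 156, which changes nothing material.

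**Step 2, formula.** With p̄ the mean of p₁ and p₂,

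n = [1.960·√(2p̄(1−p̄)) + 0.8416·√(p₁(1−p₁) + p₂(1−p₂))]² / (p₁−p₂)²

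with continuity correction n′ = (n/4)·[1 + √(1 + 4/(n·|p₁−p₂|))]².

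Example, 5% v 20%: p̄ = 0.125; 1.960 × 0.4677 + 0.8416 × 0.4555 = 0.9167 + 0.3834 = 1.3001; 1.3001² / 0.0225 = 75.1, so 76 per arm.

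**Step 3, power at 154.** Power = Φ{[0.15·√154 − 1.960·√(2p̄(1−p̄))] / √(p₁(1−p₁) + p₂(1−p₂))}. For 5% v 20%: (1.8615 − 0.9167) / 0.4555 = 2.07, so 98.1%.

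**Step 4, results for a 15-point difference** (per arm; drop-out figures divide the unrounded n by 0.88):

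| Operative v non-operative | Evaluable n | With drop-out | Evaluable n, corrected | With drop-out | Power at 154 (uncorrected) |
|---|---|---|---|---|---|
| 0% v 15% | 48 | 54 | 60 | 68 | 99.9% |
| 2% v 17% | 59 | 67 | 72 | 82 | 99.6% |
| 5% v 20% | 76 | 86 | 88 | 100 | 98.1% |
| 10% v 25% | 100 | 114 | 113 | 128 | 93.8% |
| 15% v 30% | 121 | 137 | 134 | 152 | 88.7% |
| 20% v 35% | 138 | 157 | 151 | 172 | 84.2% |
| 25% v 40% | 152 | 173 | 165 | 188 | 80.6% |

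The first four rows cover the assumed range; the last three show what happens beyond it. An exact power calculation for Fisher's test at 10% v 25% with 154 per arm gives about 92%. A one-sided test would widen the gap, because it needs fewer patients (38–79 evaluable over the first four rows, uncorrected).

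**Step 5, rates that reproduce the plan's figure.** Solving for n = 154 with a 15-point difference gives 25.9% v 40.9% uncorrected, or 21.0% v 36.0% corrected. Both need more than one plated fracture in five to fail to unite.

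**Step 6, what 154 per arm does detect.** From an assumed 15% non-operative rate, uncorrected, 80% power corresponds to 15.0% v 5.4%, a 9.6-point difference. This is solved backwards from N and is not evidence of what the planners assumed.

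**The case against.** The strongest reply is that the calculation cannot be shown wrong from its stated inputs alone. Neither arm rate is stated, a condensed article may leave them to the full protocol, and some pairs do return 175. With continuity correction, 21% v 36% does so almost exactly. The non-operative figure in the Background is open-ended, the plating evidence carries no number, and non-union appears among the historical drawbacks of surgery.

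Much of this stands. The 94–99.9% range is conditional on an operative rate of 0–10%, and the missing rates are not the finding. What does not stand is that the pairs reproducing 175 are plausible on the article's own account. An operative rate above 20% conflicts with its description of union after plating, and the article presents fixation methods as having improved since the older reports.

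A reader might also infer that the reported 15% non-union rate was mistakenly entered as the difference, with something like 15% v 5% behind N. The documents do not support that: 15% v 5% needs 140 evaluable (159 with corrected test) per arm, or about 160 and 182 after drop-out, not 175. Nor does a 15-point difference imply zero non-unions after plating, because the Background allows non-operative rates above 15%.

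**Conclusion.** The point holds conditionally. At the rates the article supports, the stated difference, power and sample size do not agree: 15 points needs about 54–128 patients per arm after drop-out, against 175 stated, so the planned number is roughly 1.4 to 3.2 times the need (175/128 to 175/54). This rests on an assumed operative non-union rate of 0–10% and a two-sided test. Even at 15% v 30% the requirement is 137 (152 corrected).

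It would be too strong to say that no rates reproduce 175, or that the trial is too small. The discrepancy runs towards more patients than the 15-point target needs, so power for that target is not at risk. The defect is a misreported figure in the justification of the primary outcome. The article does not reveal whether the difference, the power or an unstated arm rate is the one at fault.

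**What to change.** Keep 350 patients. The sponsor should retrieve the original calculation and correct the sample size section so that it states both assumed non-union rates, the test (including sidedness and any continuity correction) and the evaluable number per arm.

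- If 15 points is the target, replace the 80% with the actual power at the assumed rates, for example about 98% at 20% v 5%.
- If 80% power was planned, replace the 15 percent with the smaller difference actually used. The 9.6 points from a 15% control rate shows the order of magnitude only and should not be written in as the design basis unless the original calculation confirms it.
- If high rates such as 21% v 36% were assumed, state them and reconcile them with the Background.

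The cost is one corrected sentence, once the original calculation has been checked; enrolment does not change.

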### Statistical analysis

The research data will be reported following the CONsolidated Standards of Reporting Trial (CONSORT) [26-28]. Complication rates and recovery of function of the shoulder will be compared between the two intervention groups using the Chi-squared test. All other endpoints will be compared using co-variate analysis and student's T-test or Mann-Whitney U-test for, respectively, parametric or non-parametric data. Multivariate linear regression analysis will be performed to model the relation between binary outcome variables and treatment, adjusted for covariates. Data will be presented as mean ± SD (Standard Deviation) for parametric data or medians and percentiles (non-parametric data). P-values lower than 0.05 will be considered statistically significant. The data will be analysed using SPSS version 17 or higher (Statistical Package for the Social Sciences Inc, Chicago IL, USA).

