**Methods/design:**

A total of 350 patients will be included, between 18 and 60 years of age, with a dislocated midshaft clavicular fracture. The primary outcome is the incidence of non-union, which will be determined with standardised X-rays (Antero-Posterior and 30 degrees caudocephalad view). Secondary outcome will be the functional outcome, measured using the Constant Score. Strength of the shoulder muscles will be measured with a handheld dynamometer (MicroFET2). Furthermore, the health-related Quality of Life score (ShortForm-36) and the Disabilities of Arm, Shoulder and Hand (DASH) Outcome Measure will be monitored as subjective parameters. Data on complications, bone union, cosmetic aspects and use of painkillers will be collected with follow-up questionnaires. The follow-up time will be two years. All patients will be monitored at regular intervals over the subsequent twelve months (two and six weeks, three months and one year). After two years an interview by telephone and a written survey will be performed to evaluate the two-year functional and mechanical outcomes. All data will be analysed on an intention-to-treat basis, using univariate and multivariate analyses.

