### Outcome measures

The primary outcome is the incidence of non-union. This is determined objectively on X-rays by an independent radiologist and two surgeons, and subjectively by evaluation of the clavicular and the arm function. The function of the arm is measured with the Constant Score. The Constant score consists of four variables, reflecting both function and pain of the shoulder joint [30,31]. The subjective variables in the Constant Score are pain, activities of daily living and arm positioning. The objective variables are range of motion (ROM) without pain and strength [32]. The arm strength is measured with the MicroFET2 (Micro Force, Evaluating and Testing 2, Hoggan Health Industries Inc, West Jordan, UT, USA), a hand-held dynamometer. This device measures the force a patient can produce against the force of the examiner in Newton (N). All arm movements (i.e., retroflexion, anteflexion, abduction, adduction, endorotation and exorotation) are evaluated six weeks after initial trauma or operation in comparison with the contralateral side and thereafter at each follow-up moment. For all measurements the Make Test is used. The Make Test is characterised by the examiner holding the dynamometer stationary while the subject exerts a maximal force against the dynamometer and the examiner [33]. The results produced with the hand-held dynamometer have been shown to be reproducible, especially when measured by one single examiner at each hospital (intra-rater reliability) [33]. The inter- and intra-rater reliability of hand-held dynamometry varied in the range from good to high [34,35].

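### The analysis section matches tests to outcomes badly: a Chi-squared test for shoulder function, which is measured on numeric scales, and no fitting named test for the binary primary outcome, non-union

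*Protocol article*

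**What the plan says.** The Statistical analysis section of the protocol article allocates methods in three sentences.

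- Chi-squared test: "Complication rates and recovery of function of the shoulder will be compared between the two intervention groups using the Chi-squared test".
- Everything else: "All other endpoints will be compared using co-variate analysis and student's T-test or Mann-Whitney U-test for, respectively, parametric or non-parametric data".
- Adjusted analysis of binary outcomes: "Multivariate linear regression analysis will be performed to model the relation between binary outcome variables and treatment, adjusted for covariates".

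The only summaries it lists are mean with SD, and medians with percentiles.

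The outcomes are described elsewhere. Under Outcome measures, "The primary outcome is the incidence of non-union", and the sample size is built on a difference in non-union. The same section says "The function of the arm is measured with the Constant Score", with strength taken by a hand-held dynamometer: "This device measures the force a patient can produce against the force of the examiner in Newton (N". The Abstract adds: "Secondary outcome will be the functional outcome, measured using the Constant Score".

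**The concern.** Two outcomes carry the trial: non-union (yes or no) and shoulder function (a score). The section gives the test for categories to function and, on a literal reading, the tests for numeric data to non-union.

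For function, a Chi-squared test cannot be applied to a score as it stands. The score must first be grouped, which discards information. If that grouped comparison is the main one, it costs power.

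For non-union, the reader is not told which test decides the trial's main question. The listed summaries suit it poorly. As long as fewer than half the patients in each arm have a non-union, the median is 0 in both arms. The mean of a 0/1 variable is the proportion, but its SD adds nothing and no between-arm difference with an interval is mentioned. The one sentence that does address binary outcomes names a model meant for continuous ones.

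**Working it through.** **1. Where each outcome lands**

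| Outcome | Scale in the article | Method in Statistical analysis |
|---|---|---|
| Non-union (primary) | Binary | Not named. Literally among the other endpoints: co-variate analysis, t-test or Mann-Whitney. Adjusted: linear regression, as a binary outcome |
| Complications | Binary | Chi-squared |
| Recovery of shoulder function | Function is measured by Constant Score and strength in Newton; no categories given | Chi-squared |
| DASH, SF-36 | Scores | Other endpoints |

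Non-union is not clearly covered by complication rates. The Abstract, Rationale for the trial and Discussion list union or non-union apart from complications, and Outcome measures makes complications a secondary outcome.

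**2. Number of evaluable patients**

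From Sample size calculation: 175 per arm with 12% drop-out, so 175 × 0.88 = 154 per arm and 308 in total. The 175 itself cannot be reproduced, because only the 15-point difference is stated and not the two rates. Nothing below depends on that.

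**3. Non-union: does the choice of test change the result?**

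Simulated 0/1 data, 154 per arm, 4,000 runs, 5% two-sided; the rates are assumptions.

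| Assumed rates | t-test | Mann-Whitney | Chi-squared (uncorrected) |
|---|---|---|---|
| 15% vs 5% | 85.2% rejected | 85.2% | 85.2% |
| 10% vs 10% | 4.4% rejected | 4.4% | 4.4% |

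The unadjusted p-value is practically the same whichever test is used.

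**4. Function: cost of cutting a score in two**

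Assumptions not in the documents: a normally distributed score, a small shift between arms, and a cut at quantile p. The share of information kept is

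E = φ(z_p)² / [p(1 − p)]

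- Median split: φ(0) = 0.3989; E = 0.1592 / 0.25 = 0.637. So 308 patients act like 308 × 0.637 = 196.
- 20/80 split: φ(−0.8416) = 0.2800; E = 0.0784 / 0.16 = 0.490. So 308 act like about 151.

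Power for a standardised difference d is Φ(d√(154/2) − 1.96); after the cut, d is multiplied by √E (0.798 or 0.700).

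| Power on the full score | d | d√77 | After median split | After 20/80 split |
|---|---|---|---|---|
| 90% | 0.369 | 3.241 | Φ(2.586 − 1.96) = 73% | Φ(2.269 − 1.96) = 62% |
| 80% | 0.319 | 2.802 | Φ(2.236 − 1.96) = 61% | Φ(1.961 − 1.96) = 50% |

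A direct two-proportion calculation agrees: at an assumed d of 0.35, power falls from 86.7% to 68.5% with a cut at the mean, and to 52.2% with a cut 1 SD away from it.

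**The case against.** The strongest reply has four parts.

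*Binary outcomes are covered.* The regression sentence applies to binary outcomes, and non-union is one. A linear model on a 0/1 outcome even yields an adjusted risk difference with an interval. This stands in part: a reader might infer that the primary outcome has no analysis and that no risk difference can be had, and the text does not support that. But a linear model is a poor default for a binary outcome, since it can predict outside 0 to 1 and assumes constant variance. It also does not name the primary unadjusted test.

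*Non-union may be meant as a complication.* Current treatment concepts does list it among complications of surgery. The outcome sections keep the two apart, however, and the primary test should not hang on that reading.

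*Dichotomising the Constant Score is nowhere stated.* This is correct. A reader might infer that the score will be cut in two and not otherwise analysed. The Chi-squared sentence names recovery of function, not the Constant Score. A Chi-squared test also accepts more than two categories, and the scores themselves could be analysed with the other endpoints. What the test does require is some categorisation. The absence of a cut-point is not held against a condensed article, and nothing shows that one would be chosen after seeing the data.

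*The power figures come from outside the document.* They do rest on an assumed normal distribution, cut and effect size. The section itself allows for non-parametric data, and the trial is powered on non-union, not function. The figures show what is at risk and do not predict a loss.

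**Conclusion.** The mismatch is in the article's own text, so it is more than detail left to another document. A categorical test is assigned to function measured on numeric scales; the binary primary outcome is unnamed and literally grouped with numeric endpoints; and binary outcomes are given linear regression.

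The size differs between the two halves. For non-union the effect on the unadjusted p-value is negligible, and the defect lies in the named method and summary. For function the loss is material only if a Chi-squared test on a cut score is the main comparison. Under a normal score and 154 evaluable per arm, 64% or 49% of the information is then kept, and 90% power becomes about 73% or 62%. Overall severity is moderate: it does not invalidate the primary comparison, but it leaves both headline results with ill-matched analyses.

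**What to change.** Reword the Statistical analysis section as follows.

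1. Name non-union as the primary analysis: Chi-squared test, reported as proportions per arm and a risk difference with 95% CI. Keep Chi-squared for complications.
2. Replace linear regression for binary outcomes with logistic regression, or another model for binary outcomes, in the adjusted analysis.
3. Analyse the Constant Score, DASH and SF-36 as continuous scores with covariate adjustment.
4. Keep the Chi-squared test on recovery of function only as a supportive responder analysis, with the definition of recovery and the visit fixed in advance (the Constant Score is taken at six weeks, three months and one year).

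The cost is two or three changed sentences. No new data, visits or patients are needed.

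### The adjusted model named for binary outcomes, which on its face covers the primary outcome non-union, is linear regression with no robust standard error or risk-difference rationale

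*Protocol article*

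**What the plan says.** Under Outcome measures the protocol article states: "The primary outcome is the incidence of non-union". Each patient either has a non-union or does not, so the outcome is binary.

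Statistical analysis has three sentences on method:

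- The first assigns a chi-squared comparison to two kinds of outcome, complications and functional recovery, and does not name non-union.
- The second covers whatever is left: "All other endpoints will be compared using co-variate analysis and student's T-test or Mann-Whitney U-test", the choice between the two tests depending on whether the data are parametric.
- The third gives the adjusted model: "Multivariate linear regression analysis will be performed to model the relation between binary outcome variables and treatment, adjusted for covariates".

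No logistic or other binomial model is named anywhere. Neither is a robust standard error, nor a reason for working on the risk-difference scale. The Abstract says that both univariate and multivariate analyses will be done, so the adjusted model is a planned analysis. The article does not say whether the adjusted or the unadjusted comparison is the primary one.

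**The concern.** This is a method that the text states, not a detail left out. An analysis plan that used a logistic model would have to contradict the sentence rather than complete it.

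Ordinary linear regression assumes one residual variance for all patients. A binary outcome with risk p has variance p(1-p), which differs between the arms whenever their risks differ. Nothing in the model keeps fitted risks between 0 and 1. If non-union is rare after plating, both features matter: some fitted risks can be negative, and the standard error of the treatment effect can be wrong when the arms end up unequal in size.

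The protocol itself shows why unequal arms are worth considering. Its Background (Current treatment concepts) and its Discussion criticise the earlier randomised trial because loss to follow-up fell mainly in the non-operative arm. At stake is the accuracy of the adjusted confidence interval for non-union and other binary outcomes.

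**Working it through.** **Inputs from the protocol.** 175 patients per arm, 350 in total, a 15-point difference in non-union, and a sample size calculated "with a power (1-β) of 80 percent and a type I error (α) of 5 percent, allowing for 12 percent drop-out". Evaluable per arm: 175 × 0.88 = 154, or 308 in all.

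**Assumptions.** Arm-level risks are not stated. Background puts non-union after non-operative treatment at up to 15% and more, and describes high union rates after plating without a figure. I take 0-5% in the plate arm with a 15-point difference, and 25% v 40% as a contrasting case. The split of losses between arms is also assumed, keeping the total at the planned 12% (42 patients).

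**The plan's own figure.** 175 per arm cannot be reproduced without arm-level rates. With p̄ = (p1+p2)/2, two-sided 5% and 80% power:

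n = [1.96√(2p̄(1-p̄)) + 0.842√(p1(1-p1)+p2(1-p2))]² / 0.15², then divided by 0.88.

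- 0% v 15%: 48, giving 55
- 5% v 20%: 76, giving 87
- 25% v 40%: 152, giving 173
- 26% v 41%: 155, giving 177

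Without continuity correction, only risks near 25-26% v 40-41% come close to 175. With it, 20% v 35% gives 151, or 172 after drop-out. The point here does not depend on the sample size, but the risk level affects how large the problem is.

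**Standard error, treatment-only model.** With plate arm 1 and non-operative arm 2:

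- Ordinary: √[s²(1/n1+1/n2)], where s² = [n1p1(1-p1)+n2p2(1-p2)]/(n1+n2-2)
- True: √[p1(1-p1)/n1 + p2(1-p2)/n2]
- Coverage of a nominal 95% interval: 2Φ(1.96 × ratio) - 1

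Worked case, 168 plate and 140 non-operative, 2% v 17%. The variances are 0.0196 and 0.1411.

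- s² = (168×0.0196 + 140×0.1411)/306 = 0.0753
- Ordinary: √[0.0753 × (1/168+1/140)] = 0.0314
- True: √[0.0196/168 + 0.1411/140] = 0.0335
- Ratio 0.937, coverage 93.4%

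The interval half-width is 1.96 × 0.0314 = 6.2 points where it should be 1.96 × 0.0335 = 6.6.

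Ratio of ordinary to true standard error (coverage in brackets):

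| Evaluable, plate / non-operative | 0% v 15% | 2% v 17% | 5% v 20% | 25% v 40% | 10% v 10% |
|---|---|---|---|---|---|
| 154 / 154 | 1.003 (95.1%) | 1.003 (95.1%) | 1.003 (95.1%) | 1.003 (95.1%) | 1.003 (95.1%) |
| 161 / 147 | 0.959 (94.0%) | 0.969 (94.3%) | 0.979 (94.5%) | 0.998 (94.9%) | 1.003 (95.1%) |
| 168 / 140 | 0.916 (92.7%) | 0.937 (93.4%) | 0.955 (93.9%) | 0.992 (94.8%) | 1.003 (95.1%) |
| 175 / 133 | 0.875 (91.4%) | 0.905 (92.4%) | 0.932 (93.2%) | 0.987 (94.7%) | 1.003 (95.1%) |
| 133 / 175 | 1.151 (97.6%) | 1.113 (97.1%) | 1.080 (96.6%) | 1.020 (95.4%) | 1.003 (95.1%) |

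The 1.003 is only the degrees-of-freedom factor √(308/306).

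**Fitted risks and type I error.** These come from simulation: 3,000 runs per scenario, 308 evaluable, linear regression on treatment plus three covariates with assumed odds ratios of 1 or 2.

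- 2% v 17%: 90-99% of trials had at least one negative fitted risk, affecting 23-41% of plate-arm patients.
- 5% v 20%: 61-97% of trials, affecting 7-26% of plate-arm patients.
- 25% v 40%: negative fitted risks were rare unless covariates were strong.
- 10% v 10% (no effect): type I error 4.6-5.6%.

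**The case against.** The strongest reply is that the practical harm is small.

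- **Validity of the coefficient.** In a randomised trial the linear coefficient still estimates the risk difference, and the trial reports that contrast rather than individual predictions. This stands: negative fitted risks show a poor fit but alter no stated trial output.
- **Conclusions.** Take 15% v 2% with only 120 non-operative and 160 plate patients, a total loss of 70/350 = 20%, above the planned 12%. The interval is 6.9 to 19.1 points with the ordinary standard error and 6.3 to 19.7 with the true one (z of 4.18 v 3.78). The conclusion is the same.
- **Defensibility.** A linear risk-difference model with robust standard errors is acceptable practice. That is so, but the protocol states neither part.

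Four stronger readings are tempting and should not be made.

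1. A reader might infer that the primary result rests on this model. The protocol does not make the adjusted analysis primary.
2. A reader might infer that false-positive control suffers, or that the standard error is right only with equal arms. It is also right at any arm sizes when there is no treatment effect.
3. A reader might infer that this trial will lose more non-operative patients. The protocol says so only of the earlier trial.
4. A reader might infer that non-union has been assigned a test for scores, because the chi-squared sentence does not name it and the remaining endpoints go to the "T-test or Mann-Whitney U-test for, respectively, parametric or non-parametric data". The text is ambiguous. Background counts non-union among surgical complications, whereas the Abstract and Outcome measures list complications separately from union. It also matters little: for 14/154 v 5/154, chi-squared, Mann-Whitney and t-test give p = 0.0330, 0.0333 and 0.0331.

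**Conclusion.** The sentence is wrong as written and should be corrected: it pairs linear regression with binary outcomes and states nothing that would make that choice sound. The size of the harm is modest and conditional. With 0-5% non-union in the plate arm, a 15-point difference and the planned 12% total loss, the treatment standard error is about 2-13% too small if loss falls mainly in the non-operative arm, and about 8-15% too large in the reverse case tried (133 v 175). At 25% v 40% the error is about 2% or less. These figures rest on assumed arm-level risks and loss patterns, and the standard-error ratios are for the model without covariates. Confidence intervals and fitted risks are affected, not type I error. Severity: should-fix.

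**What to change.** In Statistical analysis, make one of two changes for binary outcomes:

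- replace linear with logistic (or another binomial) regression and report the adjusted risk difference with its 95% CI; or
- keep a linear model, but state that it estimates a risk difference and that robust standard errors will be used.

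In the same edit, name non-union explicitly among the outcomes compared by the chi-squared test, which removes the ambiguity about the unadjusted test.

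The cost is wording only, with no change to design, sample size or data collection, and it is best done before outcome data are seen. Neither model corrects bias caused by differential loss to follow-up.
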